**Methods:**

This study will be an investigator-initiated, open-label, international, multicenter, randomized controlled trial with a planned economic analysis alongside the study. Infertile women between 18 and 39 years of age, who have an ovulatory cycle, who are at low risk for tubal pathology and have been advised expectant management for at least six months (based on the Hunault prediction score) will be included in this study. Eligible women will be randomly allocated (1:1) to immediate tubal flushing (intervention) versus delayed tubal flushing (control group) by using web-based block randomization stratified per study center. The primary outcome is time to conception leading to live birth with conception within twelve months after randomization. We assess the cumulative conception rate at six and twelve months as two co-primary outcomes. Secondary outcomes include ongoing pregnancy rate, live birth rate, miscarriage rate, ectopic pregnancy rate, number of complications, procedural pain score and cost-effectiveness. To demonstrate or refute a shorter time to pregnancy of three months with a power of 90%, a sample size of 554 women is calculated.

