### Outcomes

The primary outcome is time to conception leading to live birth, with the first day of the last menstrual bleeding before a positive pregnancy test within 12 months after randomization. We will assess the presence of this endpoint also at six months after randomization as a co-primary outcome. All outcomes are listed and described in Table 1.

**Table 1 Tab1:** Outcomes and descriptions

**Primary outcome**	**Definition/measurement**
Time to conception leading to live birth measured at 6 months	Calculated from the first day of the last menstrual bleeding before a positive pregnancy test
Time to conception leading to live birth measured at 12 months	Calculated from the first day of the last menstrual bleeding before a positive pregnancy test
**Secondary outcome**	**Definition/measurement**
Biochemical pregnancy	A positive pregnancy test or serum HCG-level greater than 5 IU/L
Clinical pregnancy	Gestational sac visible on ultrasonography
Ongoing pregnancy	Positive heartbeat at 12 weeks of pregnancy on ultrasonography
Miscarriage	Non-vitality on ultrasound or spontaneous loss of pregnancy
Ectopic pregnancy	No intrauterine gestational sac with an ectopic gestational sac and/or persistent serum HCG levels
Multiple pregnancy	Pregnancy of two or more fetuses
Complications after HSG	All adverse events occurring within one month after HSG procedure, for example pelvic infection, intravasation and allergic reaction
Level of pain during HSG	Reported on VAS (scores: 0.0 to 10.0 cm)
Thyroid function after HSG	Serum FT4 and TSH one month after HSG
Used fertility treatments	IUI, IVF, ICSI
Pregnancy complications	E.g. pregnancy induced hypertension, gestational diabetes, still birth
Pregnancy outcomes	E.g. gestational age, pre-term birth, birth weight
Cost-effectiveness	Effectiveness: time to conception leading to live birth Costs: Healthcare perspective: costs for HSG and fertility treatments Societal perspective: healthcare costs, loss of productivity costs and patient costs (care services paid for by the patients themselves) using iMCQ and iPCQ

HCG: human chorionic gonadotropin, HSG: hysterosalpingography. VAS: Visual Analogue Scale, FT4: free thyroxine, TSH: thyroid-stimulating hormone, IUI: intrauterine insemination, IVF: in vitro fertilization, ICSI: intracytoplasmatic sperm injection, iMCQ: Medical Consumption Questionnaire, iPCQ: Productivity Cost Questionnaire

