### Description of intervention

Women allocated to immediate HSG will undergo their HSG preferably in the month following randomization and will subsequently have expectant management for at least six months if the HSG findings are normal.

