### Description of control

Women allocated to six-months delayed HSG will have expectant management for six months followed by undergoing HSG, if an ongoing pregnancy was not achieved in the meantime.

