### Follow-up

For the primary study, we will follow-up women for twelve months, with conception rates assessed six and twelve months after randomization. For each conception within twelve months after randomization, we will assess whether this conception leads to live birth beyond the twelve months window. Follow-up outcome data will be extracted from women’s medical records and/or by sending a digital questionnaire send to them through Castor EDC. The follow-up data include information about fertility treatments (used to calculate direct medical costs), (ongoing) pregnancy(ies) and delivery if applicable. At six and twelve months after randomization women will receive a digital questionnaire send through Castor EDC to explore indirect costs from a societal perspective during the preceding six months (iMCQ [16] and iPCQ [17]). Table 2 provides an overview of the study activities. For a secondary analysis, we will follow women until 36 months after randomization.

**Table 2 Tab2:** SPIRIT schedule of enrollment, intervention and assessments

	Study period					
	Enrollment	Allocation	Post-allocation			
TIMEPOINT	-t_1_	t_0_	t_1_	t_2_	t_3_	t_4_
ENROLLMENT:						
Eligibility screening	X					
Informed consent	X					
Allocation		X				
INTERVENTIONS:						
Immediate oil-HSG			X			
Delayed oil-HSG				X		
ASSESSMENTS:						
Baseline characteristics		X				
APAIS questionnaire*			X or X			
Pain score*			X or X			
HSG procedure, results and complications*			X or X			
iMCQ				X	X	
iPCQ				X	X	
Fertility treatment					X	
Pregnancy yes/no				X	X	
Ongoing pregnancy outcome						X

*Depending on the allocated intervention. -t_1_: prior to allocation, t_0_: at allocation, t_1_: first menstrual cycle after allocation, t_2_: 6 months after allocation, t_3_: 12 months after allocation, t_4_: 2 months post-partum

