### Sample size

The time-to-event method was used for the sample size calculation, based on the study of Dreyer et al. [9]. The expected cumulative live birth rate in the control group is 53% with a median time to event of 11 months in the control group. A two-sided log rank test with an overall sample size of 554 subjects achieves 90% power at a 0.05 significance level to or refute a statistically significant effect with a hazard radio of 1.39. It is assumed that 0.32% of the couples switch from one group to the other group. Sample size calculation was done using PASS 15.0.6 (NCSS Statistical Software LCC, Utah, USA).

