### Statistical analyses

The primary analysis will be performed according to the intention-to-treat principle. Continuous variables that are normally distributed will be summarized as means with standard deviation and, if not normally distributed, as medians with an inter-quartile range. Dichotomous data will be reported as proportions with percentages. We will summarize recruitment numbers, lost to follow-up, protocol violations and other relevant data.

The effectiveness of a fertility work-up with a strategy of immediate tubal flushing during HSG versus a strategy of six-month delayed tubal flushing during HSG will be expressed as a rate of live birth with corresponding 95% confidence intervals. Time to pregnancy will be compared in both groups using Cox Proportional-hazards analysis.

Dichotomous outcomes will be analyzed using either modified Poisson regression or logistic regression as appropriate. Continuous outcomes which are normally distributed will be analyzed using linear regression and if outcomes are non-normally distributed negative binomial regression will be used. Although p-values will be reported, the focus will be on providing Risk Ratios for effectiveness with 95% confidence intervals around them as these are more useful in interpreting the findings of the trial.

For losses to follow-up, protocol violations and missing data, we will attempt worst-case scenario analysis to explore the effect of these factors on the trial findings. As a sensitivity analysis, we will explore the effects of missing data on the trial findings using imputation techniques.

Apart from the analysis for the primary outcome – time to conception within twelve months leading to live birth - we will also perform an analysis comparing the time to conception and number of conceptions within 6 months after randomization that lead to live birth. This will allow us to assess the effect of immediate flushing with oil-based contrast as compared to no flushing.

Apart from the intention-to treat analysis, we planned a per protocol analysis. We will write a separate statistical analysis plan that will specify the details of this analysis. SPSS software (IBM) and R software (R Project for Statistical Computing) will be used for all statistical analyses.

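### If flushing works, the control HSG at month 6 makes the 12-month hazards non-proportional, so a single Cox hazard ratio would understate the time gained

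*Protocol article*

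**What the plan says.** **Outcome.** The abstract defines it thus: "The primary outcome is time to conception leading to live birth with conception within twelve months after randomization". The Outcomes section adds an earlier time point: "We will assess the presence of this endpoint also at six months after randomization as a co-primary outcome".

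**Schedule.** Under Description of intervention: "Women allocated to immediate HSG will undergo their HSG preferably in the month following randomization". Under Description of control: "Women allocated to six-months delayed HSG will have expectant management for six months followed by undergoing HSG", unless an ongoing pregnancy has been achieved. Table 2 places the delayed HSG at 6 months and ends the primary follow-up at 12 months.

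**Analysis.** Under Statistical analyses: "Time to pregnancy will be compared in both groups using Cox Proportional-hazards analysis". A later paragraph, on dichotomous and continuous outcomes, says "the focus will be on providing Risk Ratios for effectiveness with 95% confidence intervals". The section also plans a comparison of conceptions in the first 6 months, to assess flushing against no flushing.

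**Sample size.** A two-sided log-rank test with 554 women, 90% power and one effect size ("refute a statistically significant effect with a hazard radio of 1.39"). The control assumptions are 53% cumulative live birth and a median of 11 months, with 0.32% switching between groups. The abstract states the target as a time to pregnancy three months shorter.

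**The concern.** The arms differ in exposure only until the controls have their own HSG. The trial's hypothesis is that flushing raises the chance of conception. Under that hypothesis the hazard ratio exceeds 1 before month 6, then falls to about 1 if the effect lasts in both arms, or below 1 if it has faded in the immediate arm just as it begins in the controls. The change-point is part of the schedule, not an accident of conduct.

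A single Cox ratio over 12 months is then an event-weighted average of two different periods. It describes neither, and it does not convert into months gained, which is the scale of the question. The log-rank test also loses power compared with the constant-ratio case used for planning. A real but modest shortening of time to conception could come out of the 12-month comparison as a small, non-significant ratio.

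**Working it through.** **1. The plan's own figures.** An exponential median of 11 months gives 1 − 2^(−12/11) = 53.1% at 12 months, and 11/1.39 = 7.9 months, about three months shorter. The control inputs and the target therefore agree. With a constant ratio of 1.39 the immediate arm reaches 1 − 0.47^1.39 = 65.0%, a mean of 59.0% over both arms. The events needed are 4 × (1.960 + 1.282)² / (ln 1.39)² = 388, and 388/0.590 = 658 women. With 554 women there are 327 events and power is Φ(√327 × 0.3293/2 − 1.96) = 84.5%, not 90%. That gap is a separate matter. The benchmark below is thus about 84–85% for log-rank; simulation gives about 78% for restricted mean time.

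**2. Model for catch-up.** Assumptions: 277 per arm, change-point at month 6, hazard *h* unflushed and *R·h* flushed, control incidence fixed at 53% at 12 months, no dropout, later IUI not modelled. Then *h* = −ln(0.47) / [6(1 + *R*)]; for *R* = 1.39 this is 0.755/14.34 = 0.0527 per month. Two durations of effect are used:
- *Lasting*: the hazard ratio is *R* in months 0–6 and 1 in months 6–12.
- *Six months only*: the ratio is *R*, then 1/*R*.

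**3. Hand check at R = 1.39, lasting.** Six-month incidence is 27.1% v 35.5%; 12-month incidence is 53.0% v 58.4%. Events are 277 × 0.626 = 173 by month 6 and 277 × 1.114 = 309 in all, so 56.2% fall in the first period. The average log ratio is 0.562 × 0.3293 = 0.185, a hazard ratio of 1.20. Power is Φ(√309 × 0.185/2 − 1.96) = 37%.

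Restricted mean time to 12 months is (1 − e^(−6h₁))/h₁ + e^(−6h₁)(1 − e^(−6h₂))/h₂. Controls: 5.14 + 3.54 = 8.69 months. Immediate arm: 7.99 months. The gain is 0.70 month.

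**4. Results over a range.** Cox ratios are numerical limits; powers are from simulation, two-sided 0.05.

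| Flush ratio | Duration | 12-month Cox ratio | Log-rank power | Mean gain to 12 months | Restricted mean power |
|---|---|---|---|---|---|
| 1.39 | lasting | 1.20 | 35–37% | 0.70 month | about 50% |
| 1.7 | lasting | 1.33 | about 71% | 1.10 months | about 89% |
| 2.0 | lasting | 1.43 | about 89% | 1.41 months | about 98% |
| 1.39 | six months only | 1.06 | about 8% | 0.51 month | about 31% |
| 1.7 | six months only | 1.10 | about 13% | 0.82 month | about 62% |
| 2.0 | six months only | 1.13 | about 18% | 1.05 months | about 85% |

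In the six-months-only rows the two arms have the same 12-month incidence by construction (53% each), so a 12-month proportion shows nothing although time has been gained.

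**5. Sensitivity.** If the control hazard is instead ln 2/11 before the flush (control incidence then exceeds 53% at 12 months), *R* = 1.39 with a lasting effect gives a Cox ratio of 1.21 and 42.5% power. Placing the flushes at months 1 and 7 gives 1.20 and 39%. If half of the effect is lost after six months, the figures are 1.14 and 23%.

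**6. Six-month analysis.** The ratio stays at *R* throughout. At *R* = 1.39 log-rank power is about 57% (control incidence 27.1% at 6 months) to 64% (31.5%). It exceeds 90% at *R* = 1.6 with the higher incidence.

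**The case against.** **The 6-month co-primary analysis already covers the uncontaminated period.** This stands in large part. That window closes before the control HSG, so catch-up cannot distort it, and with a large flush effect it is well powered. It answers flushing versus no flushing, however. The immediate-versus-delayed question is carried by the 12-month outcome.

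**1.39 may be a strategy-level ratio.** A reader might infer that the trial has only about 36% power at 12 months. The documents do not establish this. The figure matches the abstract's three-month target and may already describe the average contrast between strategies, in which case diluting it again is wrong. The only flushed-versus-unflushed figure in the article is the Background's pregnancy odds ratio of 3.54 (2.08 to 6.02). If 20–31.5% of controls conceive by 6 months (assumed; the outcome is pregnancy, not live birth), this converts to a hazard ratio of about 2.5–2.8, or about 1.8 at the lower limit. A lasting ratio of 2.0 still gives a 12-month Cox ratio near 1.39–1.44 and about 89% power. But then 1.39 is an average over two periods, which the article does not say.

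**The risk-ratio sentence.** It might be read as making a 12-month risk ratio the main measure of the primary outcome. It sits with the dichotomous outcomes and contrasts risk ratios with p-values; time to pregnancy has its own Cox sentence. A 12-month proportion is also a legitimate comparison of strategies, since the Background hypothesises more live births. It is simply insensitive to timing.

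**Cox and log-rank remain valid under the null, and diagnostics may be in the unseen analysis plan.** Both true. The point is confined to what the article fixes: a constant-ratio sample size and one Cox comparison set against a design with a scheduled change-point.

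**Conclusion.** The point holds conditionally. If flushing has an effect, the 12-month hazards are non-proportional by design and the single Cox ratio understates the time gained. If it has none, hazards are proportional and there is no gain to miss, so it would be too strong to say that proportionality cannot hold. Nor would a gain be erased from the trial: the 6-month analysis remains, and only a short-lived effect brings the 12-month proportions level.

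The size of the loss is uncertain. Twelve-month log-rank power runs from about 36% to 89% for lasting ratios of 1.39 to 2.0, and from about 8% to 18% if the effect lasts six months. Restricted mean time does better in every catch-up case (about 50–98% and 31–85%) but does not rescue power at 1.39, and it is weaker if hazards are in fact proportional (about 78% v 84%). The results do not compel replacing the primary test or dropping the 12-month risk ratio; that is a debatable trade-off. Adding measures that show the time gained is justified.

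**What to change.** **Statistical analyses.**
- Keep the planned comparison.
- Beside it, pre-specify the difference in restricted mean time to conception leading to live birth up to 12 months, with its confidence interval.
- Report Kaplan-Meier cumulative incidence differences at 6 and 12 months.
- Report hazard ratios separately for months 0–6 and 6–12 instead of interpreting one 12-month ratio. The later ratio compares only women who have not yet conceived, so it should be read as descriptive.
- Note that the restricted mean difference is not the three-month target: even a constant ratio of 1.39 gives about 1.0 month within a 12-month window.

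**Sample size.** State whether 1.39 is the average strategy-level ratio or the flushed-versus-unflushed ratio, and give the 12-month power under control catch-up for a stated range of effect size and duration.

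**Cost.** A little more analysis with standard R code, and a less favourable stated power. Because the trial is open-label and enrolment began in August 2019, the additions should be dated and fixed before outcomes are examined by arm. No change to randomization, treatment schedule or data collection is needed.

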### Recruitment, randomization and blinding

Eligible women will be identified by their clinician during the fertility work-up. Counselling for the study will be done by a trained research staff member and all women will receive written information. Couples will be given a minimum of two days to consider participation. Those women who agree to participate will be asked to sign a written consent form. After informed consent, women will be randomly allocated to the intervention group (immediate HSG) or control group (delayed HSG). Randomization will be performed via the web-based application Castor Electronic Date Capture (EDC, Amsterdam, the Netherlands) with the use of permuted block design stratified per center (block size: 4, 6 or 8). Owing to the nature of the intervention and since our primary outcome of time to conception leading to live birth is objective, the trial is not blinded. After randomization the data will be collected in an electronic case report file (eCRF), using Castor EDC. All study procedures will be performed by clinicians and other research employees trained according to the Good Clinical Practice guidelines.

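### The primary Cox comparison names neither center nor the baseline prognostic score; adjusting for the score would add a little power without more patients

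*Protocol article*

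**What the plan says.** **Design.** The Abstract (Methods) states 1:1 allocation: "Eligible women will be randomly allocated (1:1) to immediate tubal flushing (intervention". The protocol article's section on recruitment, randomization and blinding says allocation is made "with the use of permuted block design stratified per center (block size: 4, 6 or 8". The Methods opening places the centers in the Netherlands and the United Kingdom.

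**Prognosis at entry.** According to the Abstract (Methods), eligible women "have been advised expectant management for at least six months (based on the Hunault prediction score". The Background explains that the score estimates natural conception within twelve months and that expectant management is advised when it exceeds 30%.

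**Analysis.** Under Statistical analyses: "Time to pregnancy will be compared in both groups using Cox Proportional-hazards analysis". No covariate or stratum is named, and none is ruled out.

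**Sample size.** "A two-sided log rank test with an overall sample size of 554 subjects achieves 90% power at a 0.05 significance level", for a "statistically significant effect with a hazard radio of 1.39". The control-group assumption reads "The expected cumulative live birth rate in the control group is 53" percent, "with a median time to event of 11 months in the control group". Stratification and adjustment are not mentioned here either.

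**The concern.** When randomization is balanced within a factor, the analysis would normally reflect that factor. When a baseline score predicts nearly the same event over the same twelve months, it is the obvious covariate. In a Cox model, leaving out a strong predictor gives a hazard ratio closer to 1 than the one for women of equal prognosis, and the test is less powerful than one that uses the predictor.

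This matters because the trial has little power to spare (step 1 below). It is also open-label and has enrolled since August 2019, so covariates should be chosen before outcomes are examined.

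**Working it through.** **1. The plan's own figure.** Inputs from the Sample size section: control event proportion 0.53, hazard ratio 1.39, two-sided 0.05, 90% power, 554 women. From Follow-up: twelve months per woman.

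- The control inputs agree with each other under an exponential model: 1 − 0.5^(12/11) = 0.5305.
- Treated proportion: 1 − 0.47^1.39 = 0.650. Mean: (0.53 + 0.650)/2 = 0.590.
- Events needed (Schoenfeld): 4 × (1.960 + 1.282)² / (ln 1.39)² = 388. Women needed: 388/0.590 ≈ 658. Freedman's formula gives 395 events, about 670 women.
- Events expected with 554 women: 554 × 0.590 = 327. Power: Φ(√327 × 0.3293/2 − 1.960) = Φ(1.02) ≈ 84.5%. Freedman gives 83.9%.

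The stated 90% is therefore not reproduced; an unadjusted test has about 84 to 85%.

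**2. How strong could the score be?** The documents do not say, so this is an assumption. Entry above 30% truncates the range. Suppose scores run from 30% to 60%. On the log-hazard scale the range is ln[−ln(0.40)] − ln[−ln(0.70)] = ln(0.916/0.357) ≈ 0.94. If scores are spread evenly, the SD is 0.94/√12 ≈ 0.27. A range of 0.2 to 0.4 is reasonable; 0.5 and above would need a much stronger predictor.

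**3. Simulation.** 554 women, exponential times censored at 12 months, overall control proportion 53%, conditional hazard ratio 1.39, blocks of 4, 6 or 8 within center, 1,500 trials per row. The number of centers is assumed. Monte Carlo standard error of each power is √(0.82 × 0.18/1500) ≈ 1 point. Entries are average hazard ratio / power.

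| SD score | SD center | Centers | Unadjusted | Score only | Score + center strata |
|---|---|---|---|---|---|
| 0 | 0 | 25 | 1.391 / 83.1% | 1.392 / 82.9% | 1.393 / 81.7% |
| 0.2 | 0.1 | 25 | 1.376 / 80.7% | 1.383 / 82.5% | 1.386 / 81.6% |
| 0.3 | 0.2 | 25 | 1.373 / 81.5% | 1.387 / 83.7% | 1.395 / 83.7% |
| 0.5 | 0.2 | 25 | 1.350 / 76.3% | 1.388 / 82.2% | 1.396 / 82.4% |
| 0.7 | 0.3 | 25 | 1.311 / 66.9% | 1.373 / 79.4% | 1.390 / 80.7% |
| 0.3 | 0.2 | 50 | 1.370 / 80.9% | 1.384 / 82.8% | 1.390 / 80.6% |

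At SD 0.2 to 0.3, with 25 centers, the gain from using both factors is 0.9 to 2.2 points. A further run of 700 trials per setting gave about 1 to 4 points at SD 0.27 to 0.4 (error about 1.4 points). A run of 1,000 trials with a single baseline predictor gave 83% against 84% at SD 0.25 and 80% against 85% at SD 0.4, which is consistent within simulation error.

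**4. Center by itself.** With no score effect and 25 centers, stratifying changes power from 83.2% to 82.7% at center SD 0.2, and from 80.2% to 82.4% at center SD 0.4. With 50 centers (score SD 0.3, center SD 0.2, score not in the model), stratifying by every center lowers power from 80.9% to 77.7%. Pooling small centers was not simulated.

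**5. Against the plan.** If 1.39 is the marginal hazard ratio, the natural reading of a two-group log-rank calculation, the unadjusted test keeps its 84 to 85%. Adding 1 to 4 points gives roughly 85 to 89%, still short of 90%. If 1.39 is conditional, adjustment only brings power back to about 82 to 84% in the 25-center rows with SD 0.2 to 0.3.

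**The case against.** The strongest reply is that this rests on silence. A journal article condenses the protocol, covariates are commonly left to the analysis plan, and nothing says the Cox model is unadjusted. That has real weight: the accurate statement is that the article names neither factor, not that the analysis will use neither. The article does announce a separate plan, but the sentence follows the one on the per-protocol analysis and, as worded, promises details of that analysis. It is unclear whether it reaches the primary model. What survives is a request to state a better model that uses information obtained at entry.

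The second reply is that the lower unadjusted hazard ratio is non-collapsibility, not bias. This is correct. A reader might infer that the unadjusted analysis is wrong, or that the trial loses power against its own plan. The documents do not support either. The unadjusted estimate answers a marginal question, and if 1.39 is marginal nothing planned is lost; a gain is forgone.

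Third, the score predicts natural conception, whereas the outcome is conception leading to live birth, after flushing and with fertility treatments recorded. It is therefore a related predictor and not a perfect one. Nor is it certain that it is stored as a number: Table 2 lists only baseline characteristics, and the Discussion describes prognosis-based management as particular to the Netherlands, while UK centers also recruit. Both points stand and limit the expected gain.

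**Conclusion.** The point holds as a low-cost improvement, not as an error in the plan. Adjusting for the baseline score would add roughly 1 to 4 points of power if its log-hazard SD is 0.2 to 0.4. The gain is about 6 points at 0.5 and about 14 at 0.7, but nothing in the documents supports values that high. These sizes rest on assumed SDs, an assumed number of centers, exponential times and a conditional hazard ratio of 1.39.

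Nearly all the gain comes from the score. Center should be accounted for because the randomization used it, not for power. A reader might infer that ignoring center makes the confidence intervals seriously wrong. No calculation here shows that: at center SD 0.2 power was unchanged within simulation error, and at 0.4 the difference was about 2 points.

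A reader might also infer that adjustment makes up the missing power. It does not by itself do so under the assumed range. The gap between 90% and about 84 to 85% is a separate sample-size matter.

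**What to change.** State in Statistical analyses, before outcome data are examined, that:

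- the primary Cox model adjusts for the baseline prognostic score as a continuous covariate;
- it accounts for center, with small centers pooled within country under a rule fixed in advance;
- the six-month analysis uses the same model;
- the unadjusted hazard ratio is reported as support.

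The cost is a sentence or two and no extra patients. There are two small downsides. The reported hazard ratio becomes conditional on prognosis and center, which should be said when it is interpreted. The score must also be available for every woman, so the sponsor should confirm that it is recorded as a number in both countries.

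### Negative binomial regression, a model for counts, is prescribed for non-normal continuous outcomes, so model-based confidence intervals depend on the unit of measurement and can be wrong in either direction

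*Protocol article*

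**What the plan says.** The Statistical analyses section of the protocol article sorts continuous outcomes by distribution. "Continuous outcomes which are normally distributed will be analyzed using linear regression"; for the rest, "if outcomes are non-normally distributed negative binomial regression will be used". The subject of the sentence is continuous outcomes. No restriction to counts, choice of unit or robust variance is attached to the rule.

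Table 1 (Outcomes) shows what the rule can reach:

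- pain: "Reported on VAS (scores: 0.0 to 10.0 cm", a bounded score with one decimal;
- thyroid function: "Serum FT4 and TSH one month after HSG";
- pregnancy outcomes: "E.g. gestational age, pre-term birth, birth weight", of which gestational age and birth weight are continuous.

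Only the pain score has a unit in Table 1. TSH appears in mU/L under Study population. No unit is given for gestational age, birth weight or FT4, and no mean or SD for any of the five.

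**The concern.** A negative binomial model assumes variance mu + alpha*mu^2 with alpha not below zero. The linear term makes sense for counts, where a Poisson floor exists. It has no meaning for a weight, a duration or a concentration, and two things follow.

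1. **Unit dependence.** Multiply the outcome by c. The true variance is multiplied by c^2, but the linear term only by c. Expressed in the old unit, the assumed variance is mu/c + alpha*mu^2. A change from kg to g therefore changes the fitted precision, although the data carry the same information.
2. **No room for small variance.** Where the variance is below the mean, alpha goes to zero and the model falls back to Poisson, with a standard error that is too large. With a long right tail the error can go the other way.

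The same section says that the focus will be on estimates with 95% intervals rather than on p-values, and the interval is what this rule distorts. Thyroid function and pregnancy outcomes are relevant to safety. An interval that is too wide can hide a difference, and one that is too narrow can suggest a difference that is not there.

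**Working it through.** The plan states no figure on this point, so there is none to reproduce. The check is algebra, then simulation.

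**Inputs from the protocol.** "an overall sample size of 554 subjects" with 1:1 allocation gives 277 per arm. A control live birth rate of 53% and a hazard ratio of 1.39 give the number of births:

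- control: 0.53 x 277 = 147;
- intervention: 1 - 0.47^1.39 = 0.65, and 0.65 x 277 = 180;
- average: about 164 per arm (165 used).

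**Assumed, because the documents give none of them:**

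- gestational age: mean 39.3 weeks, SD 1.3 to 3, left-skewed;
- birth weight: mean 3.4 kg, SD 0.4 to 0.6;
- TSH: mean 2 mU/L, SD 0.8 to 2.5, log-normal;
- FT4: mean 15 pmol/L, SD 2 to 3;
- pain: mean about 4.8 cm, SD about 2.4;
- about 240 HSGs per arm for pain and thyroid outcomes.

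**Step 1, algebra.** In the unadjusted two-arm log-link model, the estimate is the log ratio of the arm means. Its true variance is about 2*SD^2/(n*mean^2). When alpha is zero, the model gives 2/(n*mean). Hence, when the variance is below the mean,

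model SE / true SE = sqrt(mean)/SD.

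- Gestational age in weeks: sqrt(39.3) = 6.27. Divided by SD 1.3, 2 and 3 this is 4.8, 3.1 and 2.1.
- Gestational age in days (mean 275.1): sqrt(275.1) = 16.6. Divided by 9.1 and 14 this is 1.8 and 1.2. At SD 21 days the variance (441) exceeds the mean, so the formula no longer applies.
- Birth weight in kg: sqrt(3.4) = 1.84. Divided by 0.4, 0.5 and 0.6 this is 4.6, 3.7 and 3.1.
- FT4 in pmol/L: sqrt(15) = 3.87. Divided by 2 and 3 this is 1.9 and 1.3.
- TSH in mU/L: sqrt(2) = 1.41. Divided by 0.8 and 1 this is 1.8 and 1.4.

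**Step 2, simulation.** Null trials (1,000 to 1,500 per case), negative binomial fitted by maximum likelihood with dispersion estimated:

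| Outcome and unit | Assumed SD | Model SE / true SE | Type I error at nominal 5% |
|---|---|---|---|
| Gestational age, weeks | 1.3 / 2 / 3 | 4.8 / 3.1 / 2.1 | 0% throughout |
| Gestational age, days | same data shape | 1.9 / 1.2 / 1.0 | 0% / 2% / 5% |
| Birth weight, kg | 0.4 / 0.5 / 0.6 | 4.6 / 3.7 / 3.1 | 0% throughout |
| Birth weight, g | same data shape | 1.0 throughout | 4 to 5% |
| TSH, mU/L | 0.8 / 1 / 1.5 / 2.5 | 1.8 / 1.4 / 1.0 / 0.8 | 0.1% / 1% / 6% / 12% |
| Pain, cm | about 2.4 | about 1.0 | 4% |

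A further run of the gestational age case reached 5.1 in weeks, hence a range of about 2 to 5.

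**Step 3, what a ratio of 3 means.** A comparison with a true power of 90% keeps a power of 1 - Phi(3 x 1.96 - (1.96 + 1.28)) = 1 - Phi(2.64), about 0.4%. This is an illustration only, since the protocol claims no power for these outcomes.

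**Step 4, does a suitable method remove it?** For birth weight (SD 0.5), the negative binomial standard error of the log ratio was 0.059 in kg and 0.017 in g. A gamma model gave 0.0165 and 0.0168, and robust standard errors gave the same. The small remaining difference arises because the kg and g figures come from separately simulated data sets.

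**The case against.** Several objections have weight.

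- **Not every outcome falls under the rule.** Outcomes judged normal go to linear regression. Birth weight and FT4 may well be, and their ratios then never arise. This stands, and those figures are conditional. Gestational age and TSH are the more likely candidates for the non-normal branch.
- **Some units are harmless.** Birth weight in g and pain in cm come out near 1.0. This also stands, but validity should not hang on a unit that the plan leaves open.
- **The standard errors might be robust.** Sandwich errors would remove the unit dependence. The section does not say which kind it means. It names modified Poisson regression for dichotomous outcomes, a method that carries robust errors, but promises nothing similar here. The finding is limited to model-based errors.
- **The sentence may be loose wording for count-like data.** The number of treatment cycles would suit the model. The text, however, says continuous outcomes.
- **A separate analysis plan may settle it.** It is announced directly after the per-protocol analysis, and it may cover more. The point here is a rule that is stated wrongly, not a detail left out.

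A reader might infer that the intervals are always several times too wide, that effect estimates are biased, or that the trial's main conclusion is at risk. The documents support none of these. The ratio runs from about 0.8 to about 5 depending on outcome, unit and shape. The unadjusted ratio of means does not depend on the dispersion. The primary outcome is analysed by Cox regression.

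**Conclusion.** The concern holds in a limited form. The protocol assigns a count model to continuous outcomes that are not counts, and that is wrong as written. Unit dependence follows from the variance function and needs no assumed data; its size does. Under the SDs listed above, the largest distortion is for gestational age in weeks and, if judged non-normal, birth weight in kg, where the tests become so conservative that real differences would rarely be detected. For TSH the error can go either way. The low end is a matter of skewness that the fitted dispersion does not capture, not of the unit. Pain in cm is essentially unharmed.

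The reach is confined to model-based standard errors for secondary continuous outcomes. Gestational age and birth weight are listed only as examples, and no power is claimed for them. The sentence should be corrected before analysis, but it does not threaten the primary result.

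**What to change.** Replace the sentence in Statistical analyses. Non-normal continuous outcomes should be analysed with a method valid for continuous data. One suitable choice is linear regression with robust (sandwich) standard errors, on the log scale for right-skewed concentrations such as TSH. A gamma model with log link also removed the unit dependence in the birth weight check, so the exact choice is the team's. Reserve negative binomial regression for true counts, such as the number of treatment cycles.

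The cost is one sentence, carried into the statistical analysis plan. It needs no new data, no change to the sample size, and no software beyond the R already named.
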